## 10.2 The Number of Participants

The present study aims to show that smartphone app-delivered tinnitus therapy is not inferior to CBT in reducing tinnitus symptoms, assessed by the TFI score, after 6 months.

The required sample size was calculated based on a non-inferiority trial design with a non-inferiority margin of 13 points on the TFI scale, as used by two previous studies 9 10, and a standard deviation of 31 points. Assuming a power (1-β) of 90% and a significance level (α) of 2.5%, the sample size was determined as 90 participants per group. To account for a potential attrition rate of 10%, we increased the total sample size to 196 participants.

## 10.3 Criteria for termination of the trial

It is not anticipated that the trial will be suspended or terminated unless in the event of safety concerns or futility such as poor recruitment rates. The study may resume once concerns are addressed and with agreement from the CI, Sponsor, TSCand Ethics committee.

## 10.4 Handling of Missing and Incomplete Data

The Citrus EDC provides real-time notifications to the trial team to inform them of any missing data to minimise the risk of missing data. For patient reported outcomes, the EDC will notify the study team if assessments are overdue so the study team can follow up and collect these outcomes (the trial team will contact the patient up to 3 times). If a patient reported outcome is not completed within the scheduled window, the data will be considered missing with reasons provided. For clinician reported outcomes the EDC system will flag if an outcome is missing. Missing data will be managed according to Lindus Health SOPs. Missing data will be reported with reasons given where available and imputed using multiple imputation for the ITT population. Depending on the extent of missing values, further investigation may be made into the sensitivity of the analysis results to the method(s) specified.

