## 7.11 Early Discontinuation/Withdrawal of Participants

Each participant has the right to withdraw from the study at any time. In addition, the participant’s GP or trial Sponsor may discontinue the participation of a participant from the study at any time, if this is considered necessary for any reason including:

● Pregnancy

● Ineligibility

- Participant decision

● Inability to comply with study procedures

● Withdrawal of consent

Following participant withdrawal, no further clinical assessments will be performed. The participant will be contacted by a member of the central team and a reason for withdrawal will be requested and documented. All data recorded prior to withdrawal will be analysed in the intention-to-treat population.

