## 10.1 Description of Statistical Methods

The primary analysis will be conducted on the intention-to-treat (ITT) population. In addition to this, a per-protocol analysis will also be planned as a sensitivity analysis. Compliance will be defined as a minimum of 60 minutes of total use for the intervention group, and one or more sessions for the CBT group. Participants reporting poor compliance will be recorded and these participants will be included in the ITT analysis. Adherence to the smartphone app delivered programme will be monitored through the app with results analysed by intention-to-treat (ITT).

The primary outcome will be reduction in total TFI score at the 6 month point in the ITT population. Non-inferiority will be assessed by constructing a 95% confidence interval around the mean difference in TFI reduction between the groups, and comparing the -upper bound of the confidence interval to the pre-specified non-inferiority margin.

A secondary analysis of the primary outcome will examine significant differences between the control and intervention group’s TFI score at 6 months using a general linear model or a comparable suitable method, using the stratification variables and other potential confounding variables as covariates.

As a sensitivity analysis, the primary outcome will be analysed using the Per-Protocol (PP) population, which consists of participants complying with the treatment regimen. Compliance will be defined as a minimum of 60 minutes of total use for the intervention group, and one or more sessions of CBT for the control group.

Secondary outcomes will be compared between groups and over time with mixed-effects regression models for repeated measures, using the stratification variables and other potential confounding variables as covariates. Logistic models will be used for binary outcomes, and Gaussian models for continuous outcomes. An interim analysis may be conducted once a sufficient number of participants have completed the 6 month milestone. The results of the interim analysis do not influence the continuation of the trial.

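### Section 10.4 sets any questionnaire completed outside its visit window to missing and imputes it, so a slightly late month-6 TFI would not enter the ITT primary analysis

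*Protocol*

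**What the plan says.** Section 10.4 (Handling of Missing and Incomplete Data) sets the rule for questionnaires: "If a patient reported outcome is not completed within the scheduled window, the data will be considered missing with reasons provided". It then says how missing values are treated: "Missing data will be reported with reasons given where available and imputed using multiple imputation for the ITT population".

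Section 10.1 makes this matter for the main result. "The primary analysis will be conducted on the intention-to-treat (ITT) population", and "The primary outcome will be reduction in total TFI score at the 6 month point in the ITT population". The TFI is completed by the participant, so the rule applies to it.

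Section 10.4 also provides for overdue forms to be chased ("the trial team will contact the patient up to 3 times") and for optional further work: "Depending on the extent of missing values, further investigation may be made into the sensitivity of the analysis results to the method(s) specified". Neither sentence brings a late form back into the analysis, and I found no grace period or wider analysis window elsewhere in the protocol.

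Section 7.10.3 places the month-6 visit at week 26 +/- 14 days. The schedule of events in Appendix 2 places it at week 24, day 1, with the same tolerance.

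**The concern.** A visit window has two uses that are better kept apart. One is to say when staff should collect a form and when lateness counts as a deviation. The other is to say which scores may stand for the visit in the analysis. Section 10.4 uses one window for both. A score from a randomised participant that arrives a day or two after closure is then handled like a score that never arrived.

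Two things are at stake:

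- **Precision.** An imputed score carries less information than an observed one.
- **An avoidable assumption.** Standard multiple imputation treats late responders as exchangeable with on-time responders who have the same observed data. The trial is open-label and compares a self-paced app with scheduled therapist sessions, so lateness could depend on the arm and on how the participant is doing. The late scores are the data that would show whether the assumption holds.

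**Working it through.** **Inputs from the protocol.** SD 31, margin 13, alpha 2.5%, stated power 90%, 90 per group, 10% attrition and 196 in total (section 10.2); 1:1 allocation, so 98 per arm (section 7.6). Alpha is read as one-sided, which matches one bound of the 95% interval in section 10.1.

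**Assumptions, because the protocol gives no figure.** The share of returned month-6 forms that are late, and the share of a late form's information that imputation recovers.

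**The plan's own figure.** n per group = 2 x (31/13)^2 x (z_alpha + z_beta)^2.

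- At 90% power: 2 x 5.686 x (1.960 + 1.282)^2, which rounds up to 120.
- At 80% power: 2 x 5.686 x (1.960 + 0.842)^2, which rounds up to 90.

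The stated 90 per group therefore matches 80% power, not 90%. That is a separate matter. It enters here only because it sets the starting power.

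**Starting point with late forms kept.** 98 x 0.90 = 88.2 per arm. SE = 31 x sqrt(2/88.2) = 4.67. Power at zero true difference = Phi(13/4.67 - 1.96) = 79.5%.

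**Late forms set to missing.** Effective n = 88.2 x (1 - late share) + recovered share x 88.2 x late share. For 10% late:

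- No recovery: n = 79.4, SE = 4.92, power = Phi(13/4.92 - 1.96) = 75.2%.
- Half recovered: n = 79.4 + 0.5 x 8.8 = 83.8, SE = 4.79, power = 77.5%.

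| Late share (assumed) | Power, no recovery | Power, half recovered | 95% CI half-width, no recovery |
|---|---|---|---|
| 0% | 79.5% | 79.5% | 9.15 |
| 2% | 78.7% | 79.1% | 9.24 |
| 5% | 77.5% | 78.5% | 9.39 |
| 10% | 75.2% | 77.5% | 9.64 |
| 20% | 70.2% | 75.2% | 10.23 |

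**Bias, as illustration only.** If late responders differ by d points from on-time responders, dropping them shifts the between-arm difference by (late share in Oto - late share in control) x d. Take 15% against 5% late and d = 10: the shift is 0.10 x 10 = 1.0 point. With 88 per arm before the loss, 74.8 and 83.6 remain and the SE is 4.93.

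- If the late app users are worse, the false non-inferiority rate at a true 13-point deficit is Phi(1.0/4.93 - 1.96) = 3.9% instead of 2.5%.
- If they are better, it is Phi(-1.0/4.93 - 1.96) = 1.5%, and the shift works against Oto.

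A harsher case, 20% against 5% late with d = 15 worse, gives 0.15 x 15 = 2.25 points, SE 5.02 and 6.5%. These are complete-case values. Under imputation, d is only the part of the difference that the model does not explain, and baseline, month-1 and month-3 TFI are available to explain it.

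**The window itself.** Week 26 +/- 14 days runs from week 24 to week 28. Week 24 +/- 14 days runs from about week 22 to week 26. A form completed in week 27 is valid under section 7.10.3 and missing under Appendix 2.

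**The case against.** The strongest reply is that a pre-specified window, applied alike to both arms, is an accepted way to keep a six-month outcome at six months. Whether late scores belong in the primary or in the sensitivity analysis is partly a choice of estimand. The month-6 window is already 28 days wide and overdue forms are chased, so few may be late. Imputation recovers part of the loss and is unbiased if lateness is random given the model. All of this stands. It limits the size of the point but gives no reason to prefer an imputed score to one observed shortly after closure.

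Section 10.4 can also be read as saying that forms are not collected at all once the window closes, in which case no observed score is thrown away. The protocol does not settle this. On that reading the rule forgoes an obtainable score, and the analysis has the same gap.

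A reader might infer three stronger claims that the protocol does not support:

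- **A contradiction with section 7.11.** That section says: "All data recorded prior to withdrawal will be analysed in the intention-to-treat population". It concerns participants who withdraw and says nothing about questionnaire timing. Both sections can be followed together.
- **A rule that defeats the chasing procedure.** Chasing is there to get the form in before the window closes. The steps in section 7.1 (an alert, daily reminders for 3 days, then team contact) fit inside the window if the survey is sent on or before the target date, which is an assumption.
- **A bias towards non-inferiority.** That needs late forms to be more common in the app arm and their scores to be worse than the model predicts. The reverse pattern would count against Oto.

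**Conclusion.** The point holds in a limited form. As written, section 10.4 would replace a month-6 TFI returned shortly after the window by an imputed value in the ITT primary analysis, and nothing else in the protocol restores it. The certain consequences are some loss of precision and an added missing-data assumption. Bias is possible, with unknown sign.

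The size cannot be fixed from the protocol. If imputation recovers half of the information, the power loss is 0.4 points at 2% late, 1.0 at 5% and 2.0 at 10%. With no recovery it is 4.3 points at 10% late (79.5% to 75.2%). The false-claim rates of 3.9% and 6.5% rest on assumed late shares and assumed outcome differences, and should not be quoted as expected effects. The starting power of 79.5% comes from the sample size in section 10.2, not from this rule, but it leaves little room for further loss. The change is worth making because it is cheap and removes an assumption the trial need not make.

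**What to change.** Amend section 10.4, and carry the change into the SAP, as follows:

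- The ITT primary analysis uses every TFI form actually returned within a pre-specified analysis window around each visit. This window is wider than the scheduled one and does not overlap those of adjacent visits. The same applies to EQ-5D-5L and HUI3. The completion date is recorded.
- Multiple imputation is used only when no such form exists.
- Completion outside the scheduled window is logged as a deviation.
- The analysis restricted to in-window forms is run as a sensitivity analysis.

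The analysis window needs a stated limit. Assigning each form to its nearest visit would be too loose: the midpoint between weeks 26 and 52 is week 39, so a month-6 score could be 13 weeks late. Separately, the month-6 target in section 7.10.3 (week 26) and Appendix 2 (week 24) must be reconciled, because no window is defined until they agree.

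The cost is a few sentences and no new assessments. If survey links now close with the scheduled window, they would have to stay open to the end of the analysis window. The downside is that some scores are measured later than the nominal visit; the in-window sensitivity analysis shows whether that matters.

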# 11. HEALTH ECONOMIC EVALUATION

## 11.1 Health Economic Evaluation

A health economic evaluation forms an integral part of the trial and will be conducted from the perspectives of the NHS, personal and the society. The economic evaluation will take the form of a cost-utility analysis with a one-year time horizon using quality-adjusted life years (QALYs) as the main outcome measure. Although the clinical study has a non-inferiority design and our hypothesis is that QALYs will be similar between the Oto app and standard care, there is no prior hypothesis that costs will be similar between groups. Therefore, a standard economic evaluation framework will be used to synthesise differences in costs and QALYs between study arms using the incremental cost-effectiveness ratio (ICER)^8^.

We will follow all participants from baseline to 12 months and will collect information about the delivery of the intervention (app and standard care), primary and community health care, visits to accident and emergency (A&E) and prescribed medications. We will focus on the collection of resource utilisation related to tinnitus. Data will be collected using bespoke questionnaires that will be embedded into the Lindus Health EDC platform for participant completion at regular intervals during follow-up (weeks 12, 26 and 52). Unit costs from recognised national sources including the new NHS National Cost Collection, the Personal and Social Services Research Unit (PSSRU), and the NHS Electronic Drug Tariff will be used to value NHS health care resource use. To understand the burden beyond the health service, we will ask participants about any related out-of-pocket expenses (e.g. hearing aids, complementary and alternative paid treatments) and any time away from paid employment due to the condition.

Tinnitus is known to impair aspects of daily health-related quality of life (HRQoL) and such information will be collected in the study. For the purpose of the economic evaluation, HRQoL instruments that are preference-based are required for QALY estimation. In this study we will administer the EuroQol EQ-5D-5L and the Health Utilities Index Mark 3 (HUI3)^9^. Both questionnaires are short and the EQ-5D-5L covers descriptive levels for five dimensions (mobility, self-care, usual activities, pain/discomfort, and anxiety/depression) whereas the HUI3 covers descriptive levels for eight dimensions (vision, hearing, speech, ambulation, dexterity, emotion, cognition and pain). The health state described in each measure is converted into a single value on a scale where death is anchored at 0 and perfect health at 1 using value sets. The EuroQol EQ-5D is currently the preferred preference-based instrument to measure HRQoL in adults by the National Institute for Health and Care Excellence (NICE) and we will be using the interim 5L- > 3L mapping tool to estimate utility values^10^. To calculate utility values from HUI3 responses we will use the Canadian tariff as a UK-specific value set is currently not available. The questionnaires will be administered at baseline and at all follow-up points (weeks 4, 12, 26 and 52). QALYs for each participant over the trial period will be calculated and will be derived by estimating the area under the curve of the profile generated connecting estimates of HRQoL at each time point using linear interpolation. If necessary, any baseline imbalances in HRQoL at baseline and resulting QALYs will be adjusted using regression methods. QALYs will be derived from utility values from the EQ-5D-5L and HUI3 but the former will be used in the base case analysis.

​​To understand the burden for participants and wider society, healthcare costs will be reported separately from any out-of-pocket expenses and any societal productivity losses. When analysing continuous variables (for example costs, HRQoL scores, QALYs) means and standard deviations will be computed for each trial arm and for comparisons between trial arms, mean differences and 95% parametric confidence intervals will be used. Mean differences in costs and QALYs between study arms will be synthesised using ICERs and to facilitate interpretation, net benefit statistics will be calculated^11^. Uncertainty around net-benefits will be expressed using confidence intervals (if feasible) and cost-effectiveness acceptability curves^12^. Deterministic sensitivity analysis will be used to address uncertainty around study parameters (e.g. unit costs) not participant to sampling variation. Data completeness on resource use and HRQoL will be closely monitored on a regular basis and missing data mechanisms discussed. Multiple imputation will be implemented to handle missing data if a complete case analysis results in substantial loss of information that could bias our results^13^. All analyses will be conducted and reported in accordance with existing good practice guidelines for economic evaluation^14,15^.

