# 4 OBJECTIVES AND OUTCOME MEASURES

4.1 Randomised Controlled Trial

Primary Objective

| **Objective** | **Outcome Measure** | **Timepoint(s) of evaluation** |
| --- | --- | --- |
| Assess whether Oto’s digital tinnitus programme is as effective at reducing self-reported tinnitus severity as therapist- delivered CBT | Total TFI score | Primary outcome is total TFI score at 6 months  TFI evaluated at:  Baseline, 1, 3, 6 and 12 months |

Secondary Objectives

| Objective | Outcome Measure | Timepoint(s) of evaluation |
| --- | --- | --- |
| Assess whether Oto’s digital tinnitus programme is superior to therapist-delivered CBT in reducing self-reported tinnitus severity | Total TFI score | Total TFI score at 6 months |
| Assess the self-reported impact of Oto’s digital tinnitus programme on aspects of participants tinnitus experience | 8 Tinnitus Functional Index subscales (Intrusive, Sense of Control, Cognitive, Sleep, Auditory, Relaxation, Quality of Life and Emotional). | Baseline, 1, 3, 6 and 12 months |
| Assess the impact on overall health-related quality of life of Oto’s digital programme and therapist delivered tinnitus therapy | EuroQol EQ-5D-5L and Health Utilities Index Mark 3 (HUI3) | Baseline, 3, 6 and 12 months |
| Assess the usability of the Oto digital programme | System Usability Scale | 3 months |
| Explore participants views of the impact and usability of the two interventions | Thematic analysis of focus groups and semi structured interviews | 3, 6 and 12 months |
| Understand the health economics of the two for tinnitus | Cost-utility analysis | Over trial period covering from baseline to 12 months |
| Assess the number of adverse events between the groups | eCRF | Randomisation to 3 months |
| Assess intervention Adherence | Number of participants completing the intervention | Number of participants starting the intervention at baseline compared to those completing the intervention at 3 and 6 months |

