### 7.10.2 Month 3 (Study week 12 +/- 14 days)

To collect data to include but not limited to:

- Complete TFI questionnaire
- Complete EQ-5D-5L and HUI3 questionnaires
- Adverse events
- Complete System Usability Score (SUS)
- Complete questionnaire on primary and community healthcare appointments and A&E visits related to tinnitus since week 4
- Complete questionnaire on personal out-of-pocket tinnitus related costs, any time-off work and travel information to appointments incurred since week 4
- Any change in medication (particularly medications known to be associated with tinnitus, e.g. Aspirin, diuretics) or introduction of hearing aid

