# 23. APPENDIX 2 - SCHEDULE OF EVENTS TABLE

| **Procedure** | **Pre-screener**  Week -*N* | **Screening**  Week 1, Day 0 | **Randomisation**  Day 0 | **Baseline**  Week 1, Day 1 (+ 7 days) | **Oto App starts for 6wks / consultation for CBT booked**    Day 1 | **Month 1 Follow Up**  Week 4, Day 1 (+/- 7 days) | **Month 3 Follow Up**  Week 12, Day 1 (+/- 14 days) | **Month 6 Follow Up**  Week 24, Day 1 (+/- 14 days) | **Month 12 Follow Up**  Week 52, Day 1 (+/- 28 days) |
| --- | --- | --- | --- | --- | --- | --- | --- | --- | --- |
| Informed Consent | ✓ | ✓ |  |  |  |  |  |  |  |
| Eligibility assessment | ✓ | ✓ |  |  |  |  |  |  |  |
| Medical history | ✓ | ✓ |  |  |  |  |  |  |  |
| Demographics |  | ✓ |  |  |  |  |  |  |  |
| Tinnitus Background Survey |  |  |  | ✓ |  |  |  |  |  |
| Tinnitus Functional Index (TFI) |  |  |  | ✓ |  | ✓ | ✓ | ✓ | ✓ |
| EQ-5D-5L |  |  |  | ✓ |  |  | ✓ | ✓ | ✓ |
| HUI3 |  |  |  | ✓ |  |  | ✓ | ✓ | ✓ |
| Resource Use Questionnaire |  |  |  |  |  | ✓ | ✓ | ✓ | ✓ |
| System Usability Scale |  |  |  |  |  |  | ✓ |  |  |
| AE review |  |  |  | ✓ |  | ✓ | ✓ |  |  |
| Study Experience Questionnaire |  |  |  |  |  |  | ✓ | ✓ | ✓ |
| Adherence Data collected (eCRF) |  |  |  |  |  | ✓ | ✓ | ✓ | ✓ |

#

#

#

#

#

#

#

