- Discussion/ documentation of progress and outcome of treatment plan
- Onward referral if appropriate
- Further follow-ups can be arranged as required and according to departmental policy.

At any stage in the intervention the therapist may consider onward referral if appropriate and after discussion with the participant

This could include the following:

- Audiology: hearing aid assessment and fitting, ear level sound generator fitting/ combi device fitting or further diagnostic tests
- GP: to request counselling or a formal psychological or psychiatric referral; medication review

o Where a patient has significant anxiety or depression and is judged to be at significant risk of self-harm, the GP should be contacted immediately by phone. The patient should be made aware of this and encouraged to see their GP urgently.

o If a patient has significant anxiety and depression but is not suicidal, then discuss a local referral with their GP, or self-refer for psychology support via Improving Access to Psychological Therapies.

- ENT: further tinnitus investigations, vestibular assessment
- Physiotherapy: relaxation exercises.

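### The protocol's sections disagree on which economic data are collected at week 4, and leave early costs, hospital use and baseline utility adjustment unsettled

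*Protocol*

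**What the plan says.** **Utilities.** Section 11.1 states "The questionnaires will be administered at baseline and at all follow-up points (weeks 4, 12, 26 and 52" and derives QALYs as the area under the line joining the utilities at each time point. The objectives table in section 4.1 gives the same instruments at "Baseline, 3, 6 and 12 months". The synopsis lists follow-up at 3, 6 and 12 months.

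**Resource use.** Section 11.1 says the bespoke questionnaires are "for participant completion at regular intervals during follow-up (weeks 12, 26 and 52". At month 3, section 7.10.2 asks about "primary and community healthcare appointments and A&E visits related to tinnitus since week 4", and its question on out-of-pocket costs, time off work and travel uses the same starting point. In Appendix 2 the row "Resource Use Questionnaire" is ticked at months 1, 3, 6 and 12.

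**Scope of costs.** Section 11.1 takes NHS, personal and societal perspectives from baseline to 12 months. It names delivery of the interventions, primary and community care, A&E and prescribed medication. Appendix 3 lets control therapists refer onward, including "ENT: further tinnitus investigations, vestibular assessment".

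**Baseline utility.** Section 11.1 says: "If necessary, any baseline imbalances in HRQoL at baseline and resulting QALYs will be adjusted using regression methods".

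**The concern.** Collection times and recall windows have to be right before data are gathered. An analysis plan can choose a model later, but it cannot recover a period that no participant was asked about. Nor can the multiple imputation foreseen in section 11.1, because a period asked of nobody has no observed values to impute from.

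The first four weeks are not quiet ones. Control therapy starts within a week of randomisation (section 8.2), and all participants are advised to ask their GP for a hearing-test referral (section 7.9).

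Two further gaps bear on the same analysis. An NHS-perspective costing that names no outpatient or inpatient category may miss referrals that the control specification itself permits. And adjustment of QALYs for baseline utility depends on a condition with no stated trigger. The protocol expects QALYs to be similar between arms, so small shifts could matter to the incremental cost-effectiveness ratio.

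**Working it through.** The protocol gives no numerical result to reproduce here, so the check starts with the sections side by side.

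| Place in protocol | EQ-5D-5L and HUI3 at week 4 / month 1 | Resource-use questionnaire at week 4 / month 1 |
|---|---|---|
| Synopsis | No (3, 6, 12 months) | Not addressed |
| Section 4.1 | No (baseline, 3, 6, 12 months) | Not addressed |
| Section 7.10.1 | Not named; list is open-ended | Not named; list is open-ended |
| Section 7.10.2 | Not applicable | Presupposed: recall starts at week 4 |
| Section 11.1 | Yes | No (weeks 12, 26, 52) |
| Appendix 2 | No | Yes |

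**Utilities.** Section 11.1 stands alone in including week 4. The synopsis, section 4.1 and Appendix 2 exclude it, and section 7.10.1 does not name it. If data capture is built from Appendix 2, one of the five points that section 11.1 expects will not exist.

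**Early costs.** There are two readings.
- Appendix 2 is followed: a month-1 questionnaire covers weeks 0 to 4, and the month-3 recall continues from there. Nothing is lost.
- Sections 7.10.1 and 11.1 are followed: the first questionnaire is at week 12 and looks back to week 4. Weeks 0 to 4 are not asked about. That is 4/52 = 7.7% of the horizon and 4/12 = one third of the period before the first questionnaire.

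Under the second reading the loss covers NHS appointments, A&E visits, out-of-pocket costs, time off work and travel. It does not cover control sessions, which therapists report (section 8.2), or changes in medication and new hearing aids, which section 7.10.1 records at month 1. The baseline survey in section 7.7 asks about earlier treatment and costs already incurred, so it does not fill the gap.

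**Hospital use.** Sections 7.10.2 to 7.10.4 and 11.1 name A&E but no outpatient or inpatient category. Appendix 3 permits ENT referral from control therapy, and section 8.1 describes no matching therapist referral route in the app arm. Omitted use could therefore differ by arm. The protocol has no figure for how much.

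**Baseline utility.** Take utilities at weeks 0, 12, 26 and 52 and an assumed baseline difference δ between arms (the protocol gives none).
- If δ is gone by week 12, only the first trapezoid is affected: 0.5 × 12/52 × δ = 0.115δ QALY.
- If δ persists all year: 52/52 × δ = δ QALY.

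For an assumed δ of 0.02 the unadjusted QALY difference moves by 0.0023 to 0.02. For δ from 0.01 to 0.05 the range is 0.0012 to 0.05.

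**The case against.** **The month-1 questionnaire probably exists.** Appendix 2 ticks it, the month-3 recall makes sense only if it does, and the list in section 7.10.1 is not exhaustive. This stands: the loss of weeks 0 to 4 is conditional, and not the most natural reading. But section 11.1 is the section that governs the economic analysis, and it says otherwise.

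**A reader might infer that leaving out week-4 utilities biases the cost-utility result.** The documents do not support that. A four-point area is valid but coarser, and the same interpolation applies in both arms. Let d be the gap between the week-4 utility and the straight line from week 0 to week 12. Omitting week 4 changes an arm's QALYs by 0.5 × 12/52 × d = 0.115d, so the incremental QALY moves only by 0.115 times the between-arm difference in d. That is zero if early paths are alike, and 0.0012 to 0.0115 for assumed differences of 0.01 to 0.10. The fix below accepts the four-point curve.

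**A reader might also infer that hospital care is not asked about.** That goes too far. A&E is asked about, the bespoke form is not shown, the visit lists are open-ended, and the audiology route recommended to participants is a high-street provider. Both arms are sent to their GP, who can refer from either. What remains is that no outpatient or inpatient category is named.

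**Conditional baseline adjustment could be left to an analysis plan.** That is fair as to detail, and the present wording would allow adjustment of a visible imbalance. Still, the protocol itself makes adjustment conditional and gives no trigger, and unconditional adjustment uses data already collected.

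**Only a secondary outcome is affected.** Agreed. The primary TFI comparison is untouched.

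**Conclusion.** The point holds as an inconsistency in the economic data plan. The week-4 utility contradiction and the conflict over a month-1 resource-use questionnaire are both on the page. If sections 7.10.1 and 11.1 prevail over Appendix 2, participant-reported costs for 7.7% of a horizon meant to run from baseline to 12 months go uncollected and cannot be recovered. The absence of a named outpatient or inpatient category is a gap in the listed scope, not a contradiction; the cost difference may be biased if such use differs by arm. Conditional baseline adjustment is a weakness that costs nothing to remove. No direction or size of between-arm bias can be claimed, because the protocol gives no data on early utility paths, early costs or hospital use by arm. The QALY figures above rest on assumed differences.

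**What to change.** (a) Make section 11.1 match Appendix 2 on utilities: EQ-5D-5L and HUI3 at baseline and weeks 12, 26 and 52, with the QALY area on those points. In the same edit, settle the label of the month-6 visit, which Appendix 2 calls week 24 and sections 7.10.3 and 11.1 call week 26.

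(b) Confirm the month-1 Resource Use Questionnaire in sections 7.10.1 and 11.1, or start the month-3 recall at randomisation for both service use and personal costs. Either closes the gap; the second means a longer recall period.

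(c) Check the bespoke questionnaire and, if they are missing, add tinnitus-related hospital outpatient and inpatient items. Name these categories in section 11.1.

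(d) State that the QALY difference is always adjusted for baseline utility by regression, and delete the condition that opens that sentence.

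The cost is a minor amendment, some questionnaire wording and a slightly longer form. Item (d) needs no new data. Items (b) and (c) are worth settling first, since data not asked for cannot be recovered later.
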